### 3.11. Quality Control

To ensure the quality of this trial, the DSMB of the clinical evaluation center of the General Hospital of Ningxia Medical University will monitor regularly and strictly, consisting of informed consent, participant screening, intervention, serious EA records, statistical analysis, and data management.

### 3.12. Investigation of Adverse Events and Safety

During the acupuncture treatment, subjects will be informed about adverse events such as local bleeding, subcutaneous hematoma, or pain associated and serious adverse events such as dizziness and palpitation in advance. Any adverse events and serious adverse events during treatment will be reported in the Case Report Form (CRF) and investigated, including its type and frequency, and appropriate treatments for the associated symptoms will be provided immediately to minimize serious adverse events. If a serious adverse event occurs, the case will be reported to the Data and Safety Monitoring Board (DSMB) of the clinical evaluation center of the General Hospital of Ningxia Medical University immediately and the blinding code will be broken. If necessary, even part or all of the trial will be suspended until further instructions are expected to be available. We will pay for the treatment of the subjects with serious adverse events until recovery.

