### 2.8. Randomization and Allocation

After meeting the selection criteria, 140 eligible participants will be randomly assigned to the EA group and the CG group in a 1 : 1 allocation ratio. The random grouping sequence will be performed according to a random list of numbers generated by the randomization center of Ningxia Medical University and hidden by the opaque and closed envelope. The random sequence will be managed by specific personnel who contact no participant and are not involved in the data collection or analysis.

All participants will receive the following free services, including assessment, functional magnetic resonance imaging (both EA group and CG group), health education (both EA group and CG group), and EA treatment (only EA group) and should adhere to all assessment and treatment schedules as much as possible.

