### 2.9. Blinding

A single-blind method will be used. Outcome assessors, data manager, and statistics analyzer will be blinded to group allocation. However, participants will not be blinded because each participant knows his or her group. Therefore, the results of the assessment will be kept confidential to the participants to improve the accuracy of the test indicators and assure the objectivity and reliability of the evaluation. Blinding will be maintained during the whole study process. After completion of the statistical analysis, the blind code will be disclosed.

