### 3.5. Outcome Assessment

All outcomes will be measured by several experienced assessors who have been trained to administer these assessments and are blinded to the randomization group after the baseline visit for evaluation. Meanwhile, ensure that each subject's pre- and postevaluations are conducted by the same assessor.

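### Section 3.12 names dizziness and palpitation as serious adverse events, and any serious event automatically breaks the blinding code without disclosure being confined to the DSMB

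*Protocol article*

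**What the plan says.** Section 3.12 of the protocol article opens with what patients are told about reactions to needling: "During the acupuncture treatment, subjects will be informed about adverse events". It gives two lists. Local bleeding, subcutaneous hematoma and pain are adverse events. The second list is "serious adverse events such as dizziness and palpitation". These two symptoms are the only examples of seriousness in the article, and neither is tied to an outcome such as hospital admission or threat to life.

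The same section attaches an action to the label. When a serious adverse event occurs, the case goes to the DSMB "immediately and the blinding code will be broken". Suspension of part or all of the trial may follow.

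Section 2.9 describes the blinding that the code protects: "Outcome assessors, data manager, and statistics analyzer will be blinded to group allocation". It adds that "participants will not be blinded because each participant knows his or her group", and gives one time for disclosure: "After completion of the statistical analysis, the blind code will be disclosed". Section 3.5 says that the assessors "are blinded to the randomization group after the baseline visit for evaluation". Section 2.8 states that the random sequence is "managed by specific personnel who contact no participant and are not involved in the data collection or analysis".

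**The concern.** Dizziness and palpitation are symptoms. They may accompany a grave event, but they may also pass within minutes of needling. Calling them serious by name sets seriousness by type of symptom and not by consequence.

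Two things are at stake. The first is the safety record. Needling reactions can occur only in patients who are needled, so any inflation of the serious-event count from this source falls on the EA arm alone. The discussion (section 4) relies on the rarity of serious events to call acupuncture safe, so the count matters to the trial's own argument.

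The second is blinding. With no sham procedure and with patients aware of their group, assessor blinding is a main safeguard for a MoCA score that an assessor assigns. An automatic code break with no stated limit on who learns the group exposes that safeguard more often than it needs to.

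**Working it through.** The article states no figure on this point to reproduce, so the check compares the relevant sections.

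1. **Is the labelling deliberate?** Section 3.12 puts the two lists in one sentence, ordinary events first and serious events second. Dizziness and palpitation stand on the serious side. The words introducing the list leave it open to further events but do not remove these two.

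2. **What does the label trigger?** In section 3.12 it triggers an immediate DSMB report and a code break. The break depends on no clinical need and no judgement of relatedness. The label also feeds two other rules: dropout in section 2.7, limited there to events after which continuing is inadvisable, and possible termination in section 3.9, for serious events related to acupuncture.

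3. **Which arm is exposed?** Section 2.2 plans 70 patients per group. Table 2 gives 40 sessions and restricts electroacupuncture to the EA group.
   - EA arm: 70 x 40 = 2,800 planned needling sessions.
   - Control arm: 70 x 0 = 0.

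   This counts opportunities, not events. Controls may feel dizzy for other reasons, but not from needling.

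4. **When would a break fall?** Table 1 records adverse events during weeks 1 to 8 and places outcome assessment at week 9. A break triggered during treatment therefore comes before that patient's final MoCA. Section 3.5 also wants the same assessor before and after treatment, so replacing an assessor who had learned the group would depart from another rule.

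5. **Who needs the code?** The patient knows the group (section 2.9). The operator knows it because only EA patients are needled. Neither needs a code break for care. The roles named as blinded are outcome assessors, data manager and statistician, and none of them needs the allocation to manage an event. The DSMB does have a use for it: section 3.9 asks it to act on serious events related to acupuncture, and relatedness is hard to judge without knowing whether the patient was needled.

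6. **Is disclosure confined to the DSMB?** The DSMB is the only body named in the sentence, and the sentence concerns one case. But the DSMB is named as the recipient of the report. Nothing says that it alone learns the allocation, or that the three blinded roles stay blinded afterwards.

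**The case against.** The strongest reply has four parts.

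- **Rule and exception.** A reader might infer that sections 2.9 and 3.12 contradict each other. The documents do not support that. Section 2.9 gives the general time of disclosure and section 3.12 gives a safety exception, which is ordinary drafting. This part of the reply stands.

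- **A break has a safety use.** A reader might infer that breaking the code can only do harm. That is also too strong, because the DSMB may need the allocation to judge relatedness. What remains is that patient and operator do not need it, and that disclosure is not limited to the body that does.

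- **No bias is shown.** A reader might infer that unblinded assessors would distort the MoCA comparison. No section sends the code to an assessor. Sections 2.9, 3.5 and 3.10 keep assessors and statistician blinded, and section 2.8 keeps the sequence with people outside data collection and analysis. If the code stays with the DSMB, there is no effect on the scores. A shift could be computed only by inventing both the number of affected patients and the scoring error. This part stands in full.

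- **Illustrations and missing detail.** The two symptoms are examples in a sentence about patient information, and seriousness criteria and unblinding procedures commonly sit in a full protocol or DSMB charter that is not shown. The absence of those details is therefore no fault. But the point rests on what is printed: two symptoms placed on the serious side of an explicit contrast, and an unqualified code break tied to that label. Fuller documents could add criteria, but this text would still have to change to agree with them.

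**Conclusion.** The point holds as a minor one. Section 3.12 labels two symptoms as serious that need not be, and ties the label to an automatic code break that it does not confine to the DSMB. Followed as written, this would inflate the EA arm's serious-event record and cause avoidable code breaks before the week-9 assessment.

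The conclusion assumes that staff apply the printed examples when classifying events. The documented exposure is 2,800 planned sessions in one arm and none in the other. The article gives no rate of dizziness or palpitation, so the number of affected events cannot be estimated. No effect on the primary estimate is established. Even if every break stays within the DSMB, the mislabelling and its effect on the safety record remain.

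**What to change.** In section 3.12:

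- Class an event as serious by outcome: death, threat to life, hospital admission or its prolongation, or persistent disability.
- List dizziness and palpitation with bleeding, hematoma and pain, as serious only when they meet that criterion.
- Keep the immediate report to the DSMB.
- Replace the unqualified code break with a statement that the allocation of the single case is disclosed to the DSMB only, by the holders of the random sequence described in section 2.8, and that outcome assessors, data manager and statistician stay blinded until the analysis is complete.

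The cost is a few sentences, the seriousness field in the CRF, and the patient information if it repeats this wording. Section 3.13 reports that recruitment and intervention are still under way, so the change can still take effect. The downside is minor re-coding of any events already recorded as serious.

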### 3.13. Trial Status

The project is ongoing recruitment and intervention.

## 4. Discussion

Governor vessel is one of the important meridians of the human body, which has the function of Governor Yang Qi and regulating spirit. Baihui and Shenting are very important acupoints on the Governor vessel. Baihui is the place where Yang Qi of the Governor vessel at its peak and Shenting is the place where wisdom is concentrated. Combining the stimulation of the two acupoints can strengthen the function of regulating the Du meridian and the spirit. Considering the importance of Du Meridian, Baihui and Shenting acupoints will be mainly selected in the treatment of cognitive disorders in traditional Chinese medicine, based on previous studies [22] and a large number of literature [23, 30].

On the other hand, fewer serious adverse events indicate that acupuncture is one of the safest nonpharmaceutical treatments [31, 32]. Although the clinical effectiveness of EA in improving cognitive impairment and/or major symptoms of dementia has been established, the central mechanism of EA is not clear yet. Neuroimaging, as an effective means to explore the central mechanism of acupuncture's effects, is widely used in acupuncture research [33]. Resting-state functional connectivity of the brain network reflects the inherent and spontaneous neural activity of the brain activity pattern; it is one of the most important technologies for assessing brain function and has good clinical applicability.

Based on the previous literature, acupuncture could increase DMN connectivity with pain-, affective-, and memory-related brain areas [34, 35], but evidence in vascular cognitive impairment is lacking. For this reason, we chose EA to intervene in VCIND, to explore its clinical efficacy and central mechanism, especially the changes of brain DMN.

Some limitations of this study should be noted. First, this trial is only one RCT without follow-up; whether these patients will convert to VD in the future is uncertain. Therefore, a follow-up to track the dynamic evolution of these patients is planned. Second, there is no therapeutic comparison in our study. We only set up a blank comparison group for observation. Therefore, we plan to establish a sham acupuncture group or drug group in future studies. Third, this trial is also restricted to a single center.

In conclusion, the results of this study following the CONSORT [36] and STRICTA [24] guidelines are expected to elucidate the clinical effects and neuroimaging mechanism of EA for VCIND, providing more solid evidence for traditional Chinese medicine (TCM) practitioners to give EA treatment for VCIND. Besides, we hope that our further research study will be improved and carried out in multicentered hospitals with an expanded sample size according to these experiences.

## Figures and Tables

**Figure 1 fig1:**
[figure not shown]
The planned flowchart of the trail. EA: electroacupuncture; HE: health education; MOCA: Montreal Cognitive Assessment; AVLT: Auditory Verbal Learning Test; TAP: Test of Attentional Performance; STROOP: Stroop color-naming condition; ROCFT: Rey–Osterrieth Complex Graphics Testing; rs-fMRI: resting-state functional MRI.

**Table 1 tab1:** The study schedule for enrollment, interventions, and assessments.

Items	Before enrollment −2 to −1 week	Intervention period 1–8 weeks	Outcome assessment 9 weeks
Inclusion criteria	×		
Exclusion criteria	×		
Informed consent	×		
Baseline	×		
Randomization and allocation	×		
Intervention		×	
Baker Depression Scale test	×		
MoCA	×		×
AVLT	×		×
TAP	×		×
STROOP	×		×
ROCFT	×		×
rs-fMRI	×		×
Adverse events		×	
Reasons of dropout and withdrawals		×	

**Table 2 tab2:** STRICTA checklist (details of intervention).

	Item	Detail
1. Acupuncture rationale	(1a) Style of acupuncture	Electroacupuncture based on traditional Chinese medicine theory
	(1b) Reasoning for treatment provided, based on historical context, literature sources, and/or consensus methods, with references where appropriate	Acupuncture points to be used in this study were Baihui (GV20) and Shenting (GV24) located at the head. Based on previous studies [21] and a large number of literature [22, 23], Baihui (GV20) and Shenting (GV24) will be mainly selected as acupuncture points for VCI treatment.
	(1c) Extent to which treatment was varied	Only EA group will receive electroacupuncture treatment

2. Details of needling	(2a) Number of needle insertions per subject per session	2
	(2b) Names of points used	Baihui (GV20) and Shenting (GV24)
	(2c) Depth of insertion, based on a specified unit of measurement	0.5 inches deep
	(2d) Response sought	“De qi” sensation
	(2e) Needle stimulation	Electroacupuncture
	(2f) Needle retention time	30 minutes
	(2g) Needle type	Sterilized stainless steel needle with the 0.3 ∗ 25 mm (Suzhou Medical Supplies Factory Co., Ltd., Jiangsu, China)

3. Treatment regimen	(3a) Number of treatment sessions	40 sessions (8 consecutive weeks)
	(3b) Frequency and duration of treatment sessions	30 minutes per day, 5 days per week

4. Other components of treatment	(4a) Details of other interventions administered to the acupuncture group	(a)All participants received routine treatment with essential drugs(b)All participants will be given health education once a week
	(4b) Setting and context of treatment, including instructions to practitioners and information and explanations to patients	The study will be conducted in the General Hospital of Ningxia Medical University, and all information will be provided to the subjects

5. Practitioner background	(5) Description of participating acupuncturists	A medicine acupuncture after completing 5 years of Chinese medicine undergraduate course who has more than 5 years of clinical experience

6. Control or comparator interventions	(6a) Rationale for the control or comparator in the context of the research question, with sources that justify this choice	The control group was not treated with sham acupuncture or placebo acupuncture
	(6b) Precise description of the control or comparator. If sham acupuncture or any other type of acupuncture-like control is used, provide details as for items 1 to 3 above	None

STRICTA: Standards for Reporting Interventions in Clinical Trials of Acupuncture. EA: electroacupuncture.

## Data Availability

Data and materials are available upon request from the corresponding author.

## Abbreviations

VCIND: Vascular cognitive impairment no dementia
EA: Electroacupuncture
VD: Vascular dementia
CG: Control group
MoCA: Montreal Cognitive Assessment
AVLT: Auditory Verbal Learning Test
STROOP: Stroop color-naming condition
ROCFT: Rey–Osterrieth Complex Graphics Testing
rs-fMRI: Resting-state functional magnetic resonance imaging.
